#### Study Data:

Study questionnaires will be used for data collection. Study teams will be based within the neurology outpatient clinics; an interviewer will administer the questionnaire and will record answers on the paper questionnaire. Data captured will be entered into a Microsoft Access database by the entry clerk and double-entered to ensure accuracy. Back-up database files will be kept at the end of each data entry session. For quality control purposes, query programs will be written into the database to limit the entry of incorrect data and ensure data entry into the required fields.

#### Data Storage:

Source data in this study will include survey questionnaires and investigation results. All study documents will be kept in secure filing cabinets in the offices at Makerere University, College of Health Sciences. The principal investigator will be responsible for the security of all study documents.

#### Quality Control:

All study team members will be trained in the project objectives, methods of effective communication with study participants and collection of high-quality data. The study team will receive additional training specific to the tasks they will perform within the project, including interview techniques, administration of surveys, and completion of questionnaires. Standard Operating procedures (SOPs) will be written for project activities, and booklets of all relevant documents will be provided to each member of the project team.

#### Data analysis and Data management:

The investigators at each study site will oversee data input and quality and, working with the study statistician and epidemiologist, will oversee the quantitative data analytic procedures. The CWRU data management and statistics team will also provide data management consultation as appropriate. Rigorous development of data collection forms and staff training on properly completing and checking data collection forms will reduce errors at the point of collection. Additional data management practices before and after entry into the RedCap database will identify potential problems or outlying values and catch other errors on data collection forms. Data management staff will be responsible for tracking forms entered and performing routine data checks. Analytic data sets will be prepared using SAS 9.4

Repeated Measure Analysis of Variance. The primary outcomes of interest are quality of life (QOL) and cumulative seizure frequency. Three different analytic strategies will be used to assess AIM 1. Cumulative seizure frequency will be assessed with independent samples t-tests and linear regressions, while QOL and the secondary outcomes will be examined using repeated measures analysis of variance (RMANOVA). We will examine 2 different sets of RMANOVAs.

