### Study design

This prospective non-inferiority randomised clinical trial will be conducted at Mulago and Mbarara hospitals. Participants will be adults who meet the inclusion criteria from the epilepsy clinics at Mulago and Mbarara who will be approached to participate in the study and enrolled.

The estimated sample size for the study is 188 people with epilepsy, allowing for 20% attrition or loss by missing data, reducing the final sample to a minimum of N = 150 participants.

Based on a power analysis using G*Power 3.1.9.2121 for a 2 group by 3 time points (baseline, 13-week and 24-week follow-up) repeated measures analysis of variance (RMANOVA) with an alpha of 0.05, a power of. 80, for a sample of 150 we will be able to detect a small standardised effect size of 0.10 for the within-time effect, within the time-by-group interaction effect and a small to moderate standardised effect of 0.19 for the between-group effect.

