#### Study outcomes:

The Primary outcome will be Mean change in cumulative past 24-week seizure frequency (24 weeks prior to study baseline compared to the 24-week follow-up) and Mean change from baseline to 24 weeks in QOL. Additional secondary outcomes will include Mental health comorbidity, stigma, epilepsy self-management competency, and other relevant variables, which will be assessed using validated, standardised questionnaires.

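### The primary QOL outcome is a change to week 24, but neither arm-related test of the 2 × 3 RMANOVA described for it compares that change between arms

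*Protocol article*

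**What the plan says.** Under Study outcomes, one of the two primary outcomes is "Mean change from baseline to 24 weeks in QOL". Under Data analysis and Data management, "QOL and the secondary outcomes will be examined using repeated measures analysis of variance (RMANOVA"), and the text adds "We will examine 2 different sets of RMANOVAs" without saying what either set contains.

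The only RMANOVA whose layout is given is in the power statement under Study design: a "2 group by 3 time points (baseline, 13-week and 24-week follow-up) repeated measures analysis of variance (RMANOVA"). The settings for that calculation are stated as "with an alpha of 0.05, a power of. 80, for a sample of 150". Two detectable arm-related effects follow from it. For time and time-by-group the article reports "a small standardised effect size of 0.10 for the within-time effect, within the time-by-group interaction effect". For the comparison between arms it reports "a small to moderate standardised effect of 0.19 for the between-group effect". The sample of 150 comes from 188 randomised, "allowing for 20% attrition or loss by missing data, reducing the final sample to a minimum of N = 150 participants".

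The article does not say which of these tests decides the QOL outcome, and it names no contrast at week 24.

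**The concern.** The outcome as defined calls for one comparison: the between-arm difference in change from baseline to week 24. A 2 × 3 RMANOVA gives two F tests that involve arm, and neither is that comparison.

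- **Between-group effect.** It compares the arms on the mean of all three visits. Randomisation makes the arms equal in expectation at baseline, so that visit only dilutes the estimate.
- **Time-by-group effect.** It asks whether the arm difference varies in any way over the three visits. A difference that appears at week 13 and is gone by week 24 satisfies it.

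The second case is realistic here. The Qualitative evaluation section places the end of the SMART-U groups at 13 weeks, and the Abstract describes only telephone follow-up after that. A benefit that peaks at week 13 and fades could give a significant interaction that is then reported as success on a 24-week outcome. With no deciding test named, there would also be a choice between two p-values.

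**Working it through.** **Inputs from the article.** N = 150 analysed (75 per arm under 1:1 allocation), m = 3 visits, alpha 0.05, power 0.80, effect sizes f = 0.10 and f = 0.19.

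**Assumptions.** The article gives no correlation between visits (rho). I take 0.5, with a range of 0.3 to 0.7, equal correlations, and unit SD at each visit.

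**The plan's own figures.** The noncentral F has
- interaction: lambda = f²·N·m/(1 − rho), df 2 and 296
- between-group: lambda = f²·N·m/(1 + 2·rho), df 1 and 148

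At rho = 0.5 and 80% power, the detectable f is 0.104 (interaction) and 0.188 (between-group). These round to the stated 0.10 and 0.19. The inflation is also right: 150/0.8 = 187.5, so 188.

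**What those effects mean for QOL.** Let the arm differences at weeks 0, 13 and 24 be (0, a, b) SD, with mean D = (a + b)/3.
- Between-group f = D/2. For a sustained benefit (0, d, d), D = 2d/3, so the test estimates two-thirds of d and f = d/3. The stated f = 0.19 then needs d = 0.57 SD.
- Interaction f² = (sum of squared deviations of the three differences from D)/12. For (0, d, d), or for (0, d, 0), f = d/√18.

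**Week-13-only effect, (0, 0.5, 0).** Interaction f = 0.5/√18 = 0.118, so lambda = 0.01389 × 150 × 3/0.5 = 12.5. The rejection rate is 89% (76% at rho 0.3, 99% at rho 0.7). The between-group test rejects 24% (28% to 21%). A contrast of week-24 change rejects 5%, since there is no effect at week 24.

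**Power for a 0.40 SD benefit at week 24, 75 per arm.** The change-score test has lambda = N·d²/(4 × 2(1 − rho)) = 6.0 at rho 0.5. The baseline-adjusted contrast has lambda = N·d²/(4(1 − rho²)) = 8.0.

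| Test | Sustained (0, 0.40, 0.40) | Building (0, 0.20, 0.40) |
|---|---|---|
| Between-group | 51% (60% to 44%) | 32% (38.5% to 27.5%) |
| Interaction, 2 df | 71% (56% to 91%) | 58% (44% to 81%) |
| Change-score t test | 68% (54% to 88%) | 68% (54% to 88%) |
| Baseline-adjusted week-24 contrast | 80% (72% to 93%) | 80% (72% to 93%) |

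In each bracket the first value is for rho 0.3 and the second for rho 0.7.

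**Check on the general claim.** In an RMANOVA with two visits only (baseline and week 24), on simulated data, the interaction F equalled the squared t statistic on change scores (11.349 in both). That version tests the defined outcome exactly.

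**Missing visits, if the analysis were complete-case.** With 20% missing at week 24 and, independently, 10% to 20% at week 13, complete cases number 188 × 0.9 × 0.8 = 135 down to 188 × 0.8 × 0.8 = 120. Interaction power at f = 0.104 then falls from 80% to 75% to 70%. If everyone who misses week 13 also misses week 24, 150 remain.

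**The case against.** Four points can be made for the plan.

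1. **RMANOVA as such is not unable to test the outcome.** A reader might infer that it is. The two-visit version is identical to the change-score comparison, and a planned week-24 contrast within the 2 × 3 model would also serve. One of the two announced sets could be either. This stands. What remains is that the article names neither and describes only the 2 × 3 layout.

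2. **Power lost to the choice of RMANOVA is smaller than it looks.** A reader might credit the step from 71% to 80% in the sustained case to dropping RMANOVA. It comes from baseline adjustment: the plain change-score test has 68%, slightly below the interaction. This stands too. The interaction falls below the change-score test in the building case (58% against 68%), and the between-group test falls below it in both at rho 0.5.

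3. **Discarding of participants is not stated.** A reader might infer that the plan drops anyone with a missed visit, up to 188 − 150 = 38 people. Classical RMANOVA does use complete cases, and the reduction to 150 fits that. But the sentence can equally be ordinary inflation for attrition, no exclusion rule is given, and no SAS procedure is named. An article may leave that detail to the full protocol or the SAP. In an illustrative simulation, with 20% loss depending on week-13 QOL in one arm, the complete-case bias was 0.00 to 0.04 SD, depending on the correlation pattern.

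4. **A mixed model is not the only cure.** True: naming the contrast is the essential step. The mixed model is recommended because it also adjusts for baseline and keeps participants with only one follow-up visit.

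**Conclusion.** The concern holds in limited form. The primary QOL outcome is a change to week 24, and neither of the powered arm-related tests of the only RMANOVA described compares that change between arms. The most serious consequence is that the interaction test can reject with no week-24 effect at all, in 76% to 99% of trials under a 0.5 SD effect confined to week 13. The between-group test estimates two-thirds of a sustained effect and has 51% power where the baseline-adjusted contrast has 80%.

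These figures rest on an assumed rho of 0.3 to 0.7, equal correlations, equal SDs and 75 complete participants per arm. The mismatch itself rests on none of them. Loss of randomised participants is a conditional risk that depends on how the model is fitted; it is not something the article states. This should be settled before QOL data are analysed.

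**What to change.** State that the primary QOL test is the single between-arm contrast at week 24, two-sided at the alpha assigned to QOL. Estimate it from a mixed model for repeated measures with:

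- week-13 and week-24 QOL as outcomes
- baseline QOL, randomisation strata, visit, arm and arm-by-visit as fixed effects
- an unstructured covariance between the two follow-up visits
- all observed follow-up visits included

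With baseline QOL in the model, the arm difference at week 24 is also the adjusted difference in change from baseline. Report the week-13 contrast as supportive. Define the two sets of RMANOVAs or remove the sentence. Restate the QOL power for the week-24 contrast, with the assumed correlation. The same model can serve the continuous secondary outcomes.

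The cost is wording and one power calculation. Visits, questionnaires and sample size are unchanged, and SAS 9.4, already named for preparing the data sets, can fit the model.

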### Qualitative data analysis plan

Qualitative data analysis. Interview theme analysis will be conducted with accepted qualitative data analysis methods, including specialised software, calculation of inter-rater reliabilities, rater calibration, and systematic synthesis of findings. Additional methodologic detail is provided in the data analysis section.

#### Adverse event identification/classification:

The study investigators and/or qualified research assistants will identify adverse events. All adverse events, whether considered serious or not, will be recorded and reviewed by the study P.I.s on an ongoing basis and reported to the IRB according to local IRB policy. Serious adverse events (A.E.s) are defined as events that result in any of the following: death; a life-threatening experience; in-patient hospitalisation or prolongation of existing hospitalisation; a persistent or significant disability/incapacity; or a congenital anomaly/birth defect (or an event that may require medical or surgical intervention to prevent one of the outcomes listed above).

Seizures, as a defining hallmark of epilepsy, will be recorded if/when they occur but will not be considered either SAEs or A.E.s. All A.E.s, including all SAEs, will be reported to the IRB according to local IRB policy and to the Data Safety and Monitoring Board (DSMB). A summary report of all adverse events will be submitted annually in the report and at the end of the study.

### Data and safety monitoring Board (DSMB) and safety review plan

The study will have a DSMB composed of members who are not part of the study team. At a minimum, they will review and evaluate the accumulated data for participant safety, A.E.s, study conduct and progress every 12 months. Ad-hoc meetings might be called to evaluate unanticipated serious adverse events or any other urgent issues that are relevant and which might occur during the course of the study. The DSMB will be comprised of two clinicians with epilepsy expertise at the Uganda site, a faculty member/clinician with epilepsy expertise at the U.S. site, and a biostatistician at the U.S. site who are all not part of the study team but have extensive experience with federally funded research. The DSMB communication and oversight will be accomplished via videoconference or email communication for issues needing immediate attention.

### Ethics and Dissemination

The study will be conducted according to the Helsinki Declaration[12], the NIH Human Subjects guidelines, and the International Conference on Harmonization E6 Guideline for Good Clinical Practice [13]. Approvals from local leaders will be sought before the study activities commence in the proposed areas. The study nurses will obtain informed consent from potential participants before study procedures are initiated. A copy of the consent form will be given to the study participant. Patient identifiers at the analytic level will differ from the patient’s clinic medical record number. The files that link the patient identifiers to the study numbers will be kept in locked cabinets in the study staff offices. Only aggregate data will be presented, published, and presented such that individual patients cannot be identified. This protocol version 2 dated 29th Sept 2023 was approved by the School of Medicine, Research and Ethics Committee (SOMREC) Mak-SOMREC-2023–648 and UNCST; HS2944ES. The results of this study will be submitted for publication in peer-reviewed journals, and the key findings will be presented at national conferences.

## Discussion

This is the first randomised controlled trial of self-management education for adults with epilepsy in Uganda. The intervention has been adapted for use within the Ugandan health care provision system, and the study aims to provide qualitative and quantitative evidence of the impact of this self-management intervention on the patient’s quality of life and seizure frequency.

The study procedures outlined above are intended to perform a SMART efficacy trial in rural and urban communities while evaluating the barriers and facilitators to self-management in epilepsy.

Innovative and important aspects of the proposed project include the use of a lived experience and provider stakeholder group composed of individuals and integration of mobile services in epilepsy care in Uganda, this study method allows a focus on pragmatic epilepsy outcomes relevant to both PLWE and payers/policymakers including seizure occurrence, stigma, depression, hospitalisations, and self-harm attempts.

## Figures and Tables

**Figure 1 F1:**
[figure not shown]
Flow diagram of the study progress through the phases of a parallel randomised trial of two groups (enhanced treatment as usual and SMART-U intervention

**Table 1 T1:** Topics addressed during SMART-U sessions.

Sessions	Activities/Topic
Session 1	Orientation and introductions; Emphasise ground rules; Establishment of a therapeutic relationship; Facts and myths about epilepsy, and general epilepsy management principles
Session 2	Relationship of epilepsy and stress; Stigma and “double stigma”; Strategies to cope with stigma; Introduction to personal goal setting
Session 3	Treatments for epilepsy; Complications of epilepsy; Minimising epilepsy complications; The importance of daily routine and good sleep habits
Session 4	Problem-solving skills and the IDEA approach (Identify the problem, define possible solutions, Evaluate the solutions, Act on the best solution); Talk with your healthcare providers; Role play of communication with care providers.
Session 5	Nutrition for the best physical and emotional health; Substance abuse and its effects on epilepsy; Specific stress–management approaches
Session 6	Effects of exercise and being outdoors on physical and emotional health; Medication routines; Prioritising medication side effects and discussing it with your clinician
Session 7	Social support and using your available supports; Advocacy groups for epilepsy; A personal care plan to take care of the mind and the body
Session 8	Normalising your life in spite of having a chronic but unpredictable condition; Self-management as a lifestyle; Acknowledgment of group process; Setting the stage for ongoing illness management and recovery.

## Data Availability

No datasets were generated or analysed during the current study. All relevant data from this study will be made available upon study completion.

## Abbreviations

DSMB: Data safety monitoring board
eTAU: Enhanced Treatment As Usual
PWE: People with epilepsy
QOL: Quality of life
SMART-U: Self-Management intervention for Reducing The epilepsy burden among Ugandans
SMS: Short messaging service
CWRU: Case Western Reserve University
